## Abstract

**Background**: While primary health care (PHC)-based prevention and management of heavy drinking is clinically effective and cost-effective, it remains poorly implemented in routine practice. Systematic reviews and multi-country studies have demonstrated the ability of training and support programmes to increase PHC-based screening and brief advice activity to reduce heavy drinking. However, gains have been only modest and short term at best. WHO studies have concluded that a more effective uptake could be achieved by embedding PHC activity within broader community and municipal support.

**Protocol**: A quasi-experimental study will compare PHC-based prevention and management of heavy drinking in three intervention cities from Colombia, Mexico and Peru with three comparator cities from the same countries. In the implementation cities, primary health care units (PHCUs) will receive training embedded within ongoing supportive municipal action over an 18-month implementation period. In the comparator cities, practice as usual will continue at both municipal and PHCU levels. The primary outcome will be the proportion of consulting adult patients intervened with (screened and advice given to screen positives). The study is powered to detect a doubling of the outcome measure from an estimated 2.5/1,000 patients at baseline. Formal evaluation points will be at baseline, mid-point and end-point of the 18-month implementation period. We will present the ratio (plus 95% confidence interval) of the proportion of patients receiving intervention in the implementation cities with the proportions in the comparator cities. Full process evaluation will be undertaken, coupled with an analysis of potential contextual, financial and political-economy influencing factors.

**Discussion**: This multi-country study will test the extent to which embedding PHC-based prevention and management of alcohol use disorder with supportive municipal action leads to improved scale-up of more patients with heavy drinking receiving appropriate advice and treatment.

**Study status**: The four-year study will start on 1
^st^ December 2017.

## Introduction

### Harm done by alcohol

Alcohol is a cause of a wide range of diseases and injuries, exacerbated by occasions of heavy drinking
^1^, resulting in it ranking as the ninth leading global risk-factor in 2015 for morbidity and premature death
^2^. Ranking increases to fourth in Colombia and Peru, and fifth in Mexico
^2^, the three Latin American countries addressed in this protocol.

The clinical condition of alcohol use disorder (AUD)
^3–
5^, which includes the harmful use of alcohol, is associated with considerable disability, morbidity, and mortality
^6,
7^. Worldwide in 2015, there were 63.5 million cases of AUD
^8^ (due to more restrictive definitions, this is lower than other estimates of 95 million cases
^9^), responsible for 137,500 deaths
^10^, 6.3 million years lived with disability
^8^, and 112 million disability adjusted life years
^11^.

### Sustainable development goals

Adverse impacts from AUD and the harmful use of alcohol are aggravated by lower socio-economic status
^12^. Impacts also extend beyond the individual drinker, with considerable costs borne by families, communities, health systems, and the wider economy
^7^. A large proportion of these costs are avertable
^13^. Tackling the multiple individual and societal level harms caused by AUD and the harmful use of alcohol is a global economic and public health priority, and essential for achieving global targets of reducing deaths from non-communicable diseases by 25% between 2010 and 2025
^14^, more so as risk of exposure to harmful use of alcohol increases with increasing socio-economic status in low and middle income countries
^2^. Further, building on the global NCD framework
^15^ and the WHO global strategy
^16^, UN Sustainable Development Goals Target 3.5 is to strengthen the prevention and treatment of substance abuse, including narcotic drug abuse and harmful use of alcohol, with two proposed indicators: coverage of treatment interventions (pharmacological, psychosocial and rehabilitation and aftercare services) for substance use disorders (including AUD); and, per capita alcohol consumption
^17^.

### Heavy drinking

This protocol focuses on the prevention and management of heavy drinking, an understandable term to use when identifying at risk patients in primary health care (PHC)
^18–
21^. We base our definition of heavy drinking on the European Medicines Agency’s ‘threshold 1’, more than 60g of alcohol consumed on average a day by a man and more than 40g a day by a woman
^22^. These are the same levels as original descriptions used in global burden of disease studies
^23^. For practical purposes, we take the mid-point (50g a day) as our definition of heavy drinking. At this level of consumption, there is little difference in absolute risk (about 3.5%) of dying prematurely due to alcohol before the age of 70 years between men and women
^24^.

### Advice and treatment gap

Despite the fact that heavy drinking is one of the most important modifiable causes of premature morbidity and mortality
^25^, worldwide, although the data should be interpreted with caution, it is estimated by WHO that as many as four out of five heavy drinking individuals fail to receive the offer of appropriate advice or treatment
^26,
27^. In Mexico, the gap is nine out of ten
^28,
29^. The problem is not one of lack of effective treatment and prevention options
^30,
31^. A robust and extensive body of literature demonstrates the range of evidence-based strategies available to policy makers and practitioners seeking to reduce heavy drinking
^31,
32^. Questionnaire-based screening and brief advice programmes delivered in PHC are effective
^33^ and cost-effective
^34^ in reducing heavy drinking, even though the extent to which this evidence-base is grounded in efficacy (ideal world) or effectiveness (real world) trials is still debated in some academic circles
^35^. In addition to brief advice, treatment for AUD and harmful alcohol use include cognitive behavioural therapy and pharmacotherapy, both of which are found to be effective in reducing heavy drinking
^36–
39^. However, to date at least, these have failed to achieve widespread up-take
^31,
40,
41^.

The Organisation for Economic Co-operation and Development (OECD) has estimated that if the proportion of eligible patients receiving advice and treatment for heavy drinking increased to 30% of eligible patients, the prevalence of harmful use of alcohol could decrease by as much as 10–15% across OECD member countries, with reductions in the annual incidence of AUD of 5–14%
^40^. Large scale implementation of advice and treatment programmes can be expensive because of staff and drug costs, but has the potential of large reductions in health care expenditures, with, in some countries, advice and treatment programmes estimated to be cost saving by large margins
^40^. Such programmes would also free large numbers of working age people per year from alcohol-related diseases.

### Increasing PHC activity

Two systematic reviews
^42,
43^ and two multi-country studies
^41,
44,
45^ have demonstrated the possibility of increasing the proportion of patients screened, and screen-positive patients given advice by their PHC providers. The WHO Phase III four-country study on the identification and management of alcohol-related problems in primary care found that the odds ratios for the impact of training and support on increasing higher screening proportions (defined as 20% or more of eligible patients screened) was 2.2 (95% CI=1.3 to 3.1) and on increasing higher intervention proportions (defined as 10% or more of eligible patients screened and advice given to screen positives) was 2.8 (95% CI = 1.6 to 4.0), albeit from very low baseline levels
^45^. In the more recent five-country European ODHIN (Optimizing Delivery of Health Care Interventions) study, providing training and support to PHC providers increased the number of patients screened by 50%, and providing financial reimbursement to PHC providers increased the number of patients screened by 100%, also from low baseline levels of 6/100 consulting adult patients screened
^41^. Other evidence has suggested that the impact of financial incentives on screening and brief alcohol advice in England might have limited effects
^46^. Although incentivised practices recorded higher levels of activity than those not paid to deliver alcohol interventions, overall rates of delivery remained low.

Most work has been undertaken in high-income countries. Whilst there has been some work in low- and middle-income countries
^47^, including countries of Latin America
^48–
53^, there is an opportunity to fast-track scale-up research and practice in such countries.
^54^

### Overcoming constraints on PHC activity

To date, impacts in increasing PHC provider activity have been modest
^55^. There are two important possible reasons for this, which we address in this protocol. The first reason is that standard cut-offs for the frequently used screening instrument, AUDIT-C
^56^ (commonly five for both men and women, or five for men and four for women) to trigger advice are too low, being equivalent to an average daily alcohol consumption of about 20g of alcohol or less
^57^. Practitioners may well find themselves averse to intervening at such low levels, which would also have huge resource implications, with one in three or four patients being eligible for advice. Cut-off points for managing raised blood pressure are commonly determined by levels of blood pressure at which treatment has shown to be effective
^58^. Similarly, cut-off points for brief advice could be the baseline levels of alcohol consumption found in the randomized controlled trials that have investigated the effectiveness of PHC delivered brief advice. In the first Cochrane review of the topic, when reported, baseline levels ranged from 89 to 456g per week, with an overall mean across trials of 313g per week
^59^. At a mean of 313g per week (45g per day, a little lower than the definition of heavy drinking, 50g of alcohol per day, given above), the equivalent AUDIT-C cut off would be 8
^57^. That lower cut-offs may be inappropriate is also illustrated by the lower effect sizes found in an updated Cochrane review, where the average baseline consumption at enrolment had dropped to 183g/week
^60^. It has also been suggested that PHC providers might be more engaged in screening and giving brief advice, if screening were targeted to patients with comorbid conditions, such as depression or hypertension
^30,
61,
62^. However, to date, there is insufficient evidence for an appropriate package that deals with comorbidity to scale-up
^63^. Further, it has been shown that targeted screening misses out on the vast majority of patients that would be captured by universal screening
^64^. Given the strong associations between harmful alcohol use and depression
^65,
66^, our protocol includes screening for depression and appropriate PHC-based management
^67–
69^ or referral for those patients identified as screen positive by AUDIT-C.

The second reason for modest increases in PHC-based activity could be due to a focus on providers alone, whereas successful implementation of health interventions within complex health system demands addressing a range of underlying structural and support systems
^70^. Phase IV of the WHO study on the identification and management of alcohol-related problems in primary care
^71^, outlined a range of conclusions for enhancing the widespread uptake of screening and brief advice programmes to reduce the harmful use of alcohol: (i) training and practice-based materials need local customization that can be achieved through focus groups; (ii) reframing views about alcohol of both professionals (through training) and the public (through mass media campaigns) is essential; (iii) the establishment of a lead organization is essential, gathering endorsements from a range of organisations and individuals that are highly relevant to the aims of the work; and (iv) adequately controlled community-based studies need to be undertaken to strengthen the evidence base for achieving routine implementation
^71^. The WHO Phase IV study concluded that embedding PHC-based screening and brief advice programmes within the frame of supportive community and municipal environments might lead to improved outcomes. Experience from the US-based SAMHSA SBIRT initiative
^72^ stressed the importance of local champions and whole practice buy in for successful implementation
^73,
74^.

This protocol outlines the design of a quasi-experimental study to test the scale-up of PHC based screening and brief advice programmes to reduce heavy drinking at city level in three Latin American middle-income countries
^75^ (Colombia, Mexico and Peru), in which the prevalence of AUD is 6, 7 and 3%, respectively, and the prevalence of heavy episodic drinking is 4, 11 and 12%, respectively
^4^. We will base our action on the Institute for Healthcare Improvement’s (IHI) framework for ‘going to scale’, which designates four steps in a sequence: (1)
*Set-up*, which prepares the ground for introduction and testing of the intervention that will be taken to full scale; (2)
*Develop the Scalable Unit*, which is an early testing phase; (3)
*Test of Scale-up*, which then tests the intervention in a variety of settings that are likely to represent different contexts that will be encountered at full scale; and (4)
*Go to Full Scale*, which unfolds rapidly to enable a larger number of sites or divisions to adopt and/or replicate the intervention
^70^, see
Figure 1. We call the proposed study SCALA (Scale-up of Prevention and Management of Alcohol Use Disorder in Latin America).

**Figure 1. f1:**
[figure not shown]
Sequence of activities for going to scale. The four phases of going to scale from setting up the programme within the three cities to exploiting the validated framework and strategy through city networks, with the adoption mechanisms and support systems. PHC, primary health care.

### Aim and objectives

Driven by implementation science
^70,
76–
83^, this three-country study aims to test the extent to which embedding PHC-based screening and brief advice activity within supportive municipal action leads to improved scale-up of more patients with heavy drinking receiving appropriate advice and treatment. The study has the following objectives:
1. To deliver a tailored package for improving prevention and early identification of heavy drinking, with advice and treatment for case positives that is scalable at municipal level in a wide range of middle- income countries;2. To set-up and implement the scalable package with key stakeholders in three case study cities (scalable units) from Colombia, Mexico and Peru;3. To test the scale-up of the package for its impact on provider delivery of early identification and management;4. To identify and document the facilitators and barriers, and the organizational and resource requirements for going to full-scale, including full economic analyses; and5. To present a validated framework and strategy for going to full-scale, embedding the package into routine policy and practice, taking into account aspects of stigmatization and equity, that can be replicated globally in the future throughout municipalities.

Our hypothesis is that, by embedding the primary health care action in a community and municipal setting with added support will lead to a greater proportion of patients screened and advised for heavy drinking than achieved hitherto in implementation studies that focused on providers alone.

Countries from Latin America are selected as this is a sub-region of the world in which alcohol jumps from ninth globally to the fourth most important risk factor for morbidity and premature death
^14^. The three specific middle-income countries are chosen to represent Central (Colombia and Mexico) and Andean (Peru) Latin America. The three countries have pre-existing collaboration between the authors, who have experience in the area
^48–
53^.

## Protocol

### Design

The study is a quasi-experimental design
^84^, comparing changes in screening and brief advice, and, if relevant, referral for treatment activity, amongst primary health care units (PHCUs) in intervention cities with PHCUs in similar control cities,
Figure 2.

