### Statistical measures

The primary outcome of the study will be the proportion of consulting adult patients intervened (screened and advice given to screen positives) measured during two four-week periods midway and at the end of the 18-month scale-up period, and this will be analysed at the levels of the PHCU and provider by city type (intervention or control)
^151^. Given the rarity of the event and the resulting distribution, we will use exact inference methods for comparison of intervention vs. control cities. For further analyses, including covariates, regression models will be used, taking into consideration the hierarchical nature of the data
^152^, and characteristics at different hierarchy levels (i.e., characteristics of the PHCU, characteristics at the city level, such as patterns of drinking), and incorporating 4-week baseline period measurements as covariates. Special consideration will be given to the skewness of data by applying models, such as zero-inflated binomial regression, after testing for necessary assumptions
^153,
154^. Odds ratios will be presented with 95% confidence intervals. For any PHCU or provider that drops out during the study, outcome values for subsequent measurement points will be set at the last value obtained.

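### The design compares changes, but the primary comparison has no baseline term, so a starting difference between investigator-selected municipalities carries straight into the headline ratio

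*Protocol article*

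**What the plan says.** All references are to the Protocol article.

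- **Design:** the study is described as "comparing changes in screening and brief advice" (and referral where relevant) among primary health care units (PHCUs) in intervention and control cities.
- **Abstract:** the study is "powered to detect a doubling of the outcome measure from an estimated 2.5/1,000 patients at baseline". The result to be presented is "the ratio (plus 95% confidence interval) of the proportion of patients receiving intervention in the implementation cities with the proportions in the comparator cities". No time point is attached to that ratio. The sentence before it lists baseline, mid-point and end-point as evaluation points.
- **Statistical measures:** the primary outcome is "measured during two four-week periods midway and at the end of the 18-month scale-up period". For the primary comparison, "we will use exact inference methods for comparison of intervention vs. control cities". The next step reads "For further analyses, including covariates, regression models will be used". The 4-week baseline measurements come in there, as covariates, and odds ratios are reported.
- **Cities:** intervention and comparator municipalities are investigator-selected. Comparators were chosen for similarity on socio-economic and other characteristics that bear on drinking, health care and survival, for comparable mental health services, and for geographical separation. Confirmed technical and political consent is mentioned only for the intervention municipalities.
- **Discussion:** propensity score matching is named as a way to limit confounding. Statistical measures does not mention it.

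**The concern.** In a non-randomised comparison of three municipality pairs, the baseline window is the main protection against a difference that was there from the start. The Design sentence relies on that protection and the primary comparison does not use it.

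Such a difference is plausible. The comparability criteria do not list current screening and advice activity, which is the outcome itself, and municipalities that had already given political and technical consent may have been more engaged beforehand. A static difference in either direction could then be published as success, or could hide one. More PHCUs would narrow the interval around the wrong value without moving it.

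The contrast with a secondary outcome is telling. For patient alcohol health literacy and social norms, the Outcomes section says that changes from baseline will be compared between city types. The primary outcome has no such wording.

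**Working it through.** **1. Inputs.** From Sample size: baseline rate 2.5/1,000, target 5/1,000, 1,200 adult consultations per PHCU per month, 30 PHCUs per group, ICC 0.03. Expected baseline events per PHCU and window: 1,200 × 0.0025 = 3. Starting ratios between arms are assumptions, because the article gives no rates by city.

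**2. The two quantities.** Let r be the baseline rate in intervention cities divided by that in comparator cities, and θ the relative change in intervention cities divided by that in comparator cities.

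- Level ratio at follow-up = r × θ.
- Ratio of changes = (r × θ) / r = θ.

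The plan's own scenario has r = 1 and θ = 5/2.5 = 2. Both quantities are then 2, so the plan is consistent when the starting rates are equal.

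**3. Unequal starts.**

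| Assumed r | θ | Level ratio | Ratio of changes |
|---|---|---|---|
| 1.2 | 1 | 1.2 | 1.0 |
| 1.5 | 1 | 1.5 | 1.0 |
| 2.0 | 1 | 2.0 | 1.0 |
| 0.5 | 2 | 1.0 | 2.0 |
| 0.8 | 2 | 1.6 | 2.0 |
| 1.25 | 2 | 2.5 | 2.0 |

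With r = 0.5, a true doubling disappears from the level ratio.

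**4. Effect on a test.** With 30 × 1,200 = 36,000 consultations per group, θ = 1 and clustering ignored, a two-sided 5% comparison of levels favours the intervention with probability about 25% at r = 1.2, 69% at r = 1.4 and 94% at r = 1.6. With design effect 1 + 1,199 × 0.03 = 36.97 the figure at r = 1.4 is about 6%, but the estimate is still centred on 1.4.

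**5. Spread of the estimates.** Lognormal-Poisson simulation, 20,000 replicates, 30 PHCUs per arm, 3 expected events per PHCU-window in the comparator arm, correlation of PHCU rates over time 0.7 to 0.9, θ = 1, r = 1.5:

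- The level ratio centres on 1.5 and exceeds 1.5 in about half of the trials.
- The ratio of changes centres on 1.0. It exceeds 1.5 in about 2–8% of trials if the coefficient of variation (CV) of PHCU rates is 0.5–1.0.
- The protocol's ICC implies a much larger CV: √(0.03 × 0.9975 / 0.0025) = 3.46. There the ratio of changes exceeds 1.5 in about 18–27% of trials, with a log SD of about 0.45–0.67. It is still centred on 1.0.

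**6. Precision cost with equal starts (SD of the log ratio).** At CV 0.5: 0.20 for levels against 0.22–0.24 for changes. At CV 1.0: about 0.30 against 0.25–0.31. At CV 2.0 and 3.46 the ratio of changes was no less precise than the level ratio.

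**7. Effect measure.** Reporting odds ratios is not itself the problem at these rates: (0.005/0.995) / (0.0025/0.9975) = 2.005, against 2 for the ratio of proportions. What matters is whether baseline is in the primary estimate.

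**The case against.** The plan does not ignore baseline. It schedules hierarchical models with the baseline measurements as covariates and reports their odds ratios with confidence intervals. It selects comparators for similarity and names propensity score matching. The Abstract does not say when its ratio is formed, and ratios shown at all three evaluation points would reveal a starting difference. This is also a condensed article, and a statistical analysis plan may settle the matter. Finally, assuming a 1.5-fold start and finding a level ratio of 1.5 is an identity.

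Most of this is fair. That the Abstract's ratio uses follow-up levels only is an inference from Statistical measures. The 1.5 is an illustration. The safeguards, however, do not reach the primary comparison: the regression is placed after it, the matching is not carried into the statistical section, and the selection criteria omit the outcome. The article does state a primary comparison, and it conflicts with its own Design sentence.

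Two stronger readings are tempting but not supported:

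- A reader might infer that the doubling from baseline is a further, competing definition of the effect. It is a planning scenario. With equal starts and a stable comparator, it agrees with both other quantities.
- A reader might infer that movement in the comparator rate also distorts the level ratio. With equal starts, the level ratio and the ratio of changes are identical whatever the comparator does, and a controlled comparison should net out that movement.

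**Conclusion.** The concern holds in this form. The Design promises a comparison of changes. The primary comparison, and by inference the Abstract's headline ratio, has no baseline term, and baseline is left to secondary models. Any starting ratio r multiplies the primary ratio in full: an assumed r of 1.5 with no effect gives 1.5, against 1.0 for the ratio of changes.

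The size of the real bias is unknown because no baseline rates by city are given. The small chance (2–8%) of a misleading ratio of changes holds only for a CV of PHCU rates of 0.5–1.0. At the CV of 3.46 implied by the protocol's ICC it is about 18–27%, so the remedy removes the bias from a starting difference but not the imprecision.

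A reader might infer that the trial will report a starting difference as an effect with nothing to correct it. The planned baseline-adjusted models rule that out. The fault is which estimate comes first.

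**What to change.** In the Abstract and under Statistical measures, name one baseline-adjusted contrast as the primary estimate, with its 95% confidence interval. Either of these would serve:

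- the city-type-by-period term, that is, the follow-up/baseline rate ratio in the intervention municipality divided by the same ratio in its comparator, within country pairs; or
- the hierarchical model already planned, with the 4-week baseline measurement as covariate, moved up to primary.

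The 1.0 shown above belongs to the first option. A covariate removes a starting difference only as far as its fitted coefficient allows, and a PHCU baseline of about three expected events is noisy.

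The analysis should allow for clustering by PHCU, and the text should acknowledge that there is one municipality per arm in each country, so changes specific to a municipality cannot be separated from the intervention. Report baseline rates by arm and the unadjusted follow-up ratio as descriptive results. Either carry propensity score matching into Statistical measures, stating whether baseline activity is among the matching variables, or remove it from the Discussion.

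**Cost:** wording and no new data, since the baseline window is already to be collected. The ratio of changes relies on parallel trends, which should be stated. The interval may be slightly wider if PHCU rates differ little between units or correlate weakly over time. If the ratio of changes is chosen, the power statement should be checked against it.
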